## Abstract

**Background:**

In China, there are a growing number of young women being diagnosed with breast cancer. Fear of Cancer Recurrence (FCR) has become one of the major psychological concerns reported by young breast cancer patients. Yet, there is a lack of psychological intervention tailored for reducing FCR for Chinese young breast cancer patients. In the current study, the Fear-focused Self-compassion Therapy is developed to help Chinese young breast cancer patients to manage FCR. The therapy was developed based on FCR development theories and self-compassion related therapy. The primary objective is to evaluate the short-term and long-term effectiveness of Fear-focused Self-compassion Therapy. The secondary objective is to examine the underlying mechanisms of therapy in reducing FCR in young breast cancer patients.

**Methods:**

The Fear-focused Self-compassion Therapy consists of 8-week face to face group sessions. This study will be a randomized controlled trial with 160 Chinese young female breast cancer patients with severe FCR. Participants will be randomized to the therapy group or a usual care control group (1:1). Measurements will be completed at baseline, immediately completing intervention, 3, 6, and 12 months later. Primary outcomes are FCR severity, and secondary outcomes include symptoms of depression and anxiety, satisfaction with therapy, and cost-effectiveness of the therapy.

**Discussion:**

If successful, this study will provide an effective psychological intervention to treat FCR for young breast cancer patients in China, and illuminate the underlying mechanisms of the Fear-focused Self-compassion Therapy in reducing FCR.

**Clinical trial registration:**

ClinicalTrials.gov: NCT04965428. Registered 23rd July 2021, https://clinicaltrials.gov/ct2/show/NCT04965428?cond=fear+of+cancer+recurrence&draw=2&rank=1

## Introduction

Globally, breast cancer has become one of the highly prevalent cancers in women (1). Similarly in China, the number of women being diagnosed with breast cancer is increasing, partly because of early screening and improved medical treatments (2). It is estimated that 0.37 million Chinese women are living with and beyond breast cancer in 2018 (2). About 20% of Chinese women with breast cancer are young people aged from 18 to 40 (3). Compared with older cancer patients, younger patients concern more about cancer recurrence or cancer progress (4–6). Especially for young breast cancer patients, they are more likely to have lymph node metastasis, an advanced cancer stage, a high histological grade, and a larger mass (7). Moreover, young breast cancer patients tend to choose breast conserving therapy for the consideration of future life (8). These can increase the risks of cancer recurrence and transference, which may cause clinically significant Fear of Cancer Recurrence (FCR). FCR has been found as one of the major psychological problems in young breast cancer patients (6, 9, 10). Up to 70% of young breast cancer patients suffer from clinically significant FCR (11). Therefore, it is of great clinical relevance to offer young breast cancer patients effective psychological interventions to address FCR.

FCR is defined as the fear and worry about cancer returning or cancer progress (12). FCR can be considered as a concern that may range on a continuum from mild and short-term normal fear to severe and long-term pathological fear (5). Mild FCR is adaptive, as it can prompt patients to be alert to their body symptoms (13), and increase patients' awareness of self-protection and adherence to treatment (14). Yet, severe pathological FCR may not only cause patients' overuse of primary care that increases unnecessary healthcare cost (15), but also lead to patients' intrusive thoughts, re-experienced trauma, hypervigilance, avoidance of cancer related memory, and difficulties in future planning (16, 17). This may negatively influence patients' quality of life, prognosis, and even survival (18).

Psychological interventions have been applied to reduce severe FCR in cancer patients (19–21). In particular, several RCTs have demonstrated the efficacy of psychological interventions for improving FCR, including mindfulness interventions (22–24), psychological education (25), cognitive behavioral therapy (26), and meta-cognitive therapy (27). Based upon previous empirical research, Tauber et al. conducted a meta-analysis and found that existing psychological interventions can improve FCR but to a small extent (Hedges's *g* = 0.28 – 0.33) (28). Moreover, only a few studies have tailored psychological interventions for young breast cancer patients to reduce FCR (21, 29). This calls for future studies to develop and test more effective interventions for addressing FCR (28).

To develop tailored psychological interventions to effectively address severe FCR, it is important to consider the development process of FCR into interventions. Up till now, previous research has developed several theoretical models explaining the development process of FCR including cognitive processing model (30), cognitive schema model of FCR (31), and cognitive-affective model (32). Although these models differed on components in the formulation of FCR, these models agree upon that cancer patients' cognitive evaluation about cancer recurrence plays a key role in the development of severe FCR (31). Specifically, when facing cancer-related stimulus in daily life (i.e., physical symptoms and anti-cancer advertisements), cancer patients are likely to have a dysfunctional cognitive evaluation, including catastrophizing of cancer recurrence, rumination of cancer-related traumatic memories and attentional bias to cancer related stimulus, which may cause FCR. Therefore, to help cancer patients to address severe FCR, it is needed to correct cancer patients' dysfunctional cognitive evaluation.

Self-compassion refers to treating oneself with kindness and warm when confronting with life stressors (33). Higher levels of self-compassion can help people relieve from pain and sufferings and cope with life traumas (e.g., cancer) with a tolerant, empathetic, and kind attitude (33). By treating oneself with kindness, people can adjust one's dysfunctional cognitive evaluations (e.g., rumination and catastrophizing) toward stressful events (34). There have been several empirical studies confirmed a link between high levels of self-compassion and low levels of rumination and catastrophizing (35, 36). Also, an experimental study has found that when inducing one's self-compassion with a writing task, people presented a greater ease in disengaging from negative stimuli, which clearly showed the impact of self-compassion on changing one's attentional process (37). Moreover, it is proposed that automatic nervous system (including the parasympathetic and the sympathetic nervous systems) plays an important role in self-compassion improving psychological wellbeing (38). Improved self-compassion has been found to relate to improved psychological symptoms through improved functioning of autonomic nervous system, with decreased salivary alpha amylase (i.e., indicator of sympathetic nervous system functioning) and increased heart rate variability (i.e., the index of parasympathetic nervous system functioning) (39, 40). Therefore, it can be hypothesized that improved self-compassion may lead to better psychological outcomes by adjusting one's attentional bias, dysfunctional cognitive evaluation, and the autonomic nervous system (i.e., the parasympathetic and the sympathetic nervous systems).

More recently, self-compassion related therapy (such as compassion-focused therapy and mindful self-compassion therapy), aiming to enhance self-compassion and help individuals better cope with stressful life events (38, 41), has been shown to increase the levels of self-compassion (Hedges's *g* = 0.75), and reduce symptoms of depression (Hedges's *g* = 0.66), anxiety (Hedges's *g* = 0.57), and stress (Hedges's *g* = 0.67) (42). With unique Eastern Buddhist characteristics, self-compassion related therapy involves a part of mindful meditation and aims to encourage individuals to keep self-kind and self-understanding to relieve stress when facing stressful events.

In the context of cancer, the beneficial role of self-compassion on psychological outcomes (including symptoms of depression, anxiety, and fatigue) has been confirmed in Chinese cancer patients (43, 44). As for FCR, intervention studies have started to examine the feasibility of self-compassion therapy in the application of coping with FCR (45, 46). Using randomized controlled trails, two studies focused on middle aged and elderly breast cancer patients, and confirmed that an 8-week self-compassion intervention was feasible and acceptable for these patients to decrease levels of FCR by enhancing one's self-compassion (45, 46). Yet, given the inclusion of middle aged and elderly breast cancer patients from the Western countries and the use of small sample size, it remains unclear to what extent their conclusions can be generalized into young breast cancer patients in China. Moreover, the two previous studies only examined the short-term (i.e., no longer than 6 months) efficacy of self-compassion related therapy on FCR, and it remains unknown about the long-term (i.e., longer than 6 months, such as 12 months after intervention) effectiveness and why self-compassion related therapy would be effective in reducing severe FCR.

### Aims of this study

In the current study, the Fear-focused Self-compassion Therapy, aiming to help Chinese young breast cancer patients to address FCR, has been developed. The primary aim of the current randomized controlled trial is to evaluate the effectiveness (i.e., both short-term and long-term effectiveness) and cost-effectiveness of Fear-focused Self-compassion Therapy in reducing severe FCR in young women with breast cancer, compared to usual care. Due to a lack of research comparing the cost-effectiveness between compassion-based therapy and usual care, it is hard to hypothesize which condition would be more cost-effective. This study expects that Fear-focused Self-compassion Therapy would be more cost-effective than usual care by reducing patients' FCR more effectively. Several specific hypotheses were outlined:

FCR severity would reduce to a larger extent in the Fear-focused Self-compassion Therapy condition (intervention group) compared to the treatment as usual condition (control group) from baseline and follow-up (3 months after treatment). The improvements in FCR can maintain at least 6 months after treatment.Symptoms of depression and anxiety would reduce to a larger extent in the Fear-focused Self-compassion Therapy condition compared to the treatment as usual condition from baseline and follow-up (3 months after treatment). These effects can maintain at least 6 months after treatment.Fear-focused Self-compassion Therapy would be cost-effective compared to treatment as usual.

The secondary aim of this study is to examine the underlying mechanisms of Fear-focused Self-compassion Therapy in reducing severe FCR. Specifically, the current research assumed that patients' improved dysfunctional cognitive evaluations and improved functioning of autonomic nervous system would play mediating roles between Fear-focused Self-compassion Therapy and improved FCR. Specific hypotheses are:

Fear-focused Self-compassion Therapy can increase cancer patients' levels of self-compassion, then improve cognitive evaluation processes (i.e., decreased catastrophic expectation to cancer recurrence, less attentional bias toward cancer-related stimulus, and less rumination), and reduce levels of FCR.By improving levels of self-compassion, Fear-focused Self-compassion Therapy could improve the functioning of sympathetic nervous system (with decreased salivary alpha amylase as physiological index) and parasympathetic nervous system (with increased heart rate variability as physiological index), and decrease levels of FCR.

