### Study design

The current study will compare Fear-focused Self-compassion Therapy with usual care in young women with breast cancer. A sample of 160 young female breast cancer patients with clinically significant FCR will be recruited from Shaanxi Provincial Cancer Hospital in Xi'an, China. After checking the eligibility of participants and completed the baseline measurement (T0), they will be randomized to either the Fear-focused Self-compassion Therapy or usual care control group. Four follow-up measurements will take place for both groups: immediately completing intervention (T1), after 3 months (T2), after 6 months (T3), and after 12 months (T4).

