**Secondary outcomes:**
Salivary alpha amylase	Nipro salivary alpha amylase analyzer	√	√			
HRV	MP150-Biopac data acquisition system	√	√			
Attentional bias for FCR	The dot-probe task	√	√			
Rumination	CERQ-RS	√	√			
Catastrophizing	CERQ-CS	√	√			
Psychological symptoms	HADS	√	√	√	√	√
Self-compassion	SCS	√	√	√	√	√
Quality-adjusted life year	EQ-5D	√	√	√	√	√
Healthcare consumption	MCQ	√	√	√	√	√
Process outcomes			√			

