### Statistical analyses

The aim of the primary analysis is comparing the Fear-focused Self-compassion Therapy group with usual care control group on the score of FCRI severity subscale. In the primary analysis, post-treatment scores will be compared between two groups at four measurement time points (T1, T2, T3, and T4). Analysis will be performed by using linear mixed models, including baseline scores, sociodemographic and medical variables as covariates.

The aim of secondary analysis is to test the mediating role of improved dysfunctional cognitive evaluation and improved functioning of autonomic nervous system between Fear-focused Self-compassion Therapy and improved FCR. Analysis will be performed by using multilevel structural equation model, including baseline scores, sociodemographic and medical variables as potential covariates.

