### Strengths and weaknesses

This RCT of Fear-focused Self-compassion Therapy has several strengths. First, given that most of previous research focused on middle aged and elderly cancer patients, this study could fill the knowledge of the application of Fear-focused Self-compassion Therapy in young breast cancer patient population. Second, this study examines the long-term effectiveness of Fear-focused Self-compassion Therapy for patients' FCR, to verify whether this intervention is valid for controlling FCR in a long period of time. Third, by verifying the mediating role of dysfunctional cognitive evaluation and autonomic nervous system, this study will find the underlying mechanisms of Fear-focused Self-compassion Therapy for FCR, and provide implication for future research to develop more targeted intervention. Finally, this study will promote the implementation of Fear-focused Self-compassion Therapy for patients' FCR in Chinese background and investigate whether Chinese cancer patients could benefit from this therapy. However, in the present study without the third group with other intervention, it is not allowed to compare the effectiveness of Fear-focused Self-compassion Therapy with other intervention (i.e., mindfulness-focused therapy and cognitive behavior therapy).

Considering the lack of intervention research for young breast cancer patients, this study will contribute to the knowledge about how to decrease FCR in this population. Research into long-term effective psychological treatment for this population will be of great clinical value.

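### The schedule cannot show that self-compassion changes before cognition or autonomic function, although both mechanism hypotheses say it does

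*Protocol article*

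**What the plan says.** The protocol article, under Aims of this study, sets a general secondary aim: better cognitive evaluation and "improved functioning of autonomic nervous system would play mediating roles between Fear-focused Self-compassion Therapy and improved FCR". Two specific hypotheses follow, and both are ordered. In the first, the therapy raises "levels of self-compassion, then improve cognitive evaluation processes", after which FCR falls. In the second, "By improving levels of self-compassion, Fear-focused Self-compassion Therapy could improve the functioning of sympathetic nervous system" and parasympathetic function, again with a fall in FCR.

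Table 2 fixes the measurements. "The dot-probe task" (attentional bias), the rumination and catastrophizing subscales (CERQ), salivary alpha amylase and heart rate variability are ticked at T0 and T1 only. The SCS and the Fear of Cancer Recurrence Inventory (FCRI) are ticked at T0 to T4. Under Study design, T1 is the end of therapy and T2, T3 and T4 come at 3, 6 and 12 months. No measurement falls within the eight weeks of therapy.

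Under Statistical analyses, the mediation model is given this task: "test the mediating role of improved dysfunctional cognitive evaluation and improved functioning of autonomic nervous system between Fear-focused Self-compassion Therapy and improved FCR". Self-compassion is not among the mediators named. On method, the section says: "Analysis will be performed by using multilevel structural equation model, including baseline scores, sociodemographic and medical variables as potential covariates". Under Strengths and weaknesses, the article says that "this study will find the underlying mechanisms of Fear-focused Self-compassion Therapy for FCR".

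**The concern.** A serial chain makes a claim about order: self-compassion moves, cognition or autonomic function follows, FCR follows that. Randomization protects the effect of therapy on each variable. It does not protect the links between the variables, because nobody is randomized to a level of self-compassion. For those links the order has to come from the timing of the measurements, and here the first mediator and the second are first seen after baseline at the same visit.

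A positive serial result could therefore arise because the therapy moved both mediators side by side, or because better cognition raised self-compassion. The trial could report a confirmed sequence that its data do not contain. The analysis section adds to the difficulty by leaving out the variable that heads both chains.

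**Working it through.** **1. Plan's own figures.** The plan states no figure for the mediation analysis. Its sample size concerns the FCR comparison and is used below only as an input. A two-sample t-test with d = 0.49, two-sided alpha 0.05 and power 0.80 needs 66.35, so 67 per arm and 134 in total, as stated. Adding 20% gives 134 × 1.2 = 161, close to the stated 160.

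**2. Schedule against hypotheses (Table 2).**

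| Variable | Post-baseline values | When |
|---|---|---|
| Self-compassion (SCS) | 4 | T1, T2, T3, T4 |
| Rumination, catastrophizing, attentional bias | 1 each | T1 |
| Amylase, heart rate variability | 1 each | T1 |
| FCR (FCRI) | 4 | T1, T2, T3, T4 |

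- Self-compassion to cognition or autonomic function: the earliest post-baseline SCS is T1 and the latest mediator value is T1. Usable lags: 0.
- Cognition or autonomic function to FCR: T1 precedes T2, T3 and T4. Usable lags: 3.

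**3. What a positive serial test would mean.** The documents give no path values, so those below are assumptions. N = 160 × 0.8 = 128 completers, 64 per arm, 4,000 trials per case. A is arm (0/1), S self-compassion, C cognition, F FCR at T2, each e an independent standard normal error unless stated, and r the link between the mediators (0.3, 0.5, 0.7). In every case F = 0.4C + √(1 − 0.4²)e.

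- Hypothesized chain: S = 0.6A + e; C = rS + √(1 − r²)e.
- Parallel change: S = 0.6A + e₁; C = 0.6A + e₂; corr(e₁, e₂) = r.
- Reverse order of mediators: C = 0.6A + e; S = rC + √(1 − r²)e.

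The test regresses S on A, C on A and S, and F on A, S and C. It is positive if A→S, S→C and C→F all have |t| > 1.979.

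| Truth | r = 0.3 | r = 0.5 | r = 0.7 |
|---|---|---|---|
| Hypothesized chain | 86% | 91% | 85% |
| Parallel, no serial effect | 86% | 90% | 86% |
| Reverse order | 17% | 39% | 61% |

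The test does not separate the chain from parallel change, even with FCR taken at T2.

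**4. The simpler path.** In the same runs, therapy → C → F was detected in 91% to 92% of trials when therapy acted directly on cognition. If therapy reaches cognition only through self-compassion, its effect on C is 0.6r (0.18, 0.30, 0.42) and detection was 17%, 38% and 66%. The path is estimable, but its power depends on the mechanism.

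**5. Choice of FCR time point.** Assumed: 160 patients, therapy effect 0.49 SD, equal links of 0.5 or 0.8, and FCR at T2 = 0.7 × FCR at T1 plus error.

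- Fully reversed truth (therapy → FCR at T1 → cognition → self-compassion): the serial test was falsely positive in about 13% (links 0.5) to 51% (links 0.8) of trials. This was the same with T1 or T2 FCR as outcome, and fell to 1% to 3% when T2 FCR was adjusted for T1 FCR.
- True chain completed during therapy: detection was about 85% to 87% with T2 FCR unadjusted, and about 5% after adjustment for T1 FCR. Adding a small late effect of cognition on T2 FCR (0.15) still left adjusted detection below half.

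Moving the outcome to T2 does not by itself remove reverse causation. Adjusting for T1 FCR removes most of it, along with any effect already achieved by T1.

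**The case against.** The strongest reply is that the secondary aim as worded, and the analysis as planned, ask only whether cognition and autonomic function mediate between therapy and FCR. For that question the schedule does supply an order, since the T1 mediators precede three later FCRI waves. This stands. A reader might infer that the whole secondary aim is lost, or that no mediator can be placed before FCR. The documents support neither reading.

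A second reply is that the article condenses a fuller protocol, so its silence on lags, on the FCRI time point for mediation and on T1 adjustment is missing detail and not error. This also stands, and nothing here rests on that silence. In particular, the text does not say that T1 FCRI is the mediation outcome, so one cannot say that every link is cross-sectional. The missing measurement is different, because no analysis plan can supply it.

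Third, a reader might infer that the reverse order fits the data equally well. Under the assumptions above it does not: it gives positive results less often (17% to 61%) than the true chain (85% to 91%). It is parallel change that the test fails to distinguish.

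Finally, adjustment for T1 FCRI might seem the natural cure. It lowers false positives, but it also conditions on a variable that lies on the path if the chain acts during therapy, so it cannot serve as the main analysis.

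**Conclusion.** The point holds for one link in each chain: self-compassion to cognition, and self-compassion to autonomic function. In both, the only post-baseline mediator values coincide with the first post-baseline SCS, so the stated order cannot be separated from parallel change or from the reverse. This follows from Table 2 and the visit schedule and needs no assumption. The simulated percentages do rest on assumed path values and show only how misleading a positive serial test could be.

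The broader mediation question and the primary comparison are unaffected. The two specific hypotheses and the promise to find the underlying mechanisms go further than the schedule allows. They should be changed, either by adding a measurement or by narrowing the claim.

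**What to change.** Choose one of three options.

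- **Mid-therapy measure.** Collect the 26-item SCS once around mid-therapy in both arms, ideally with the two 4-item CERQ subscales (26 + 8 = 34 items). The SCS then precedes the T1 cognitive and autonomic values. The CERQ items show whether rumination or catastrophizing had already moved. Cost: one short questionnaire and an extra contact with control patients.
- **Repeat at T2.** Add the eight CERQ items at T2, so that T1 SCS precedes them. To keep the chain in order, the FCR outcome would then be T3 or later. Cost: eight items at an existing visit. This does not order the dot-probe, amylase or heart rate variability links.
- **No new data.** Drop the ordering between self-compassion and the other mediators, withdraw the statement that the study will find the underlying mechanisms, and report the serial link as associational. Cost: a weaker mechanism claim.

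Under any option, name self-compassion in the secondary analysis if the chains are kept, and use FCRI severity at T2 or later as the mediation outcome. Show adjustment for T1 FCRI only as a sensitivity analysis, with a note that it removes any effect achieved by T1. Better timing still does not exclude unmeasured common causes of the mediators and FCR, so the conclusions should be worded accordingly.
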